### Procedures

Sample recruitment will have the support of the clinical staff of the outpatient clinics based on inclusion and exclusion criteria. All eligible participants will be asked to fill out the informed consent. Participants will be randomized at a 1:1 ratio to receive usual care composed by CR alone (control group) or the mHeart.4U program (intervention group). Treatment allocation will follow a computer-generated schedule prepared by a biostatistician. The randomization schedule will be stratified by gender and trial center and will use random permuted blocks (Figure 1). The control group will follow the standard treatment protocol (27), while the Intervention group will, additionally, participate in the mHEART.4U intervention (Figure 1).

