### Outcomes and Measurements

Outcome measurements will be carried out at the 3-month (T1) and the 6-month interventions (T2) (Table 1).

**Table 1 T1:** Schedule of assessments.

**Assessments**	**Measure**	**T0**	**T1**	**T2**
Recurrent cardiovascular event				
Cardiovascular	Patient health records		x	x
Rehospitalization	Death certificates			
Cardiovascular urgent visit				
Unplanned revascularization				
Cardiovascular mortality				
Worsening heart failure				
Quality of Life	MacNew heart disease health-related Quality of life questionnaire	x	x	x
Adherence to treatment	Therapeutic self-care scale	x	x	x
Anthropometric measures	Patient health records (BMI, waist circumference)	x	x	x
Nutrition	Health-promoting lifestyle profile-II	x	x	x
Physical activity	Health-promoting lifestyle profile-II	x	x	x
Clinical data	Patient health records	x	x	x
Blood pressure, heart rate,	Systematic coronary risk evaluation			
blood biomarkers, pathological				
history, cardiovascular risk				
Sociodemographic Data	Sociodemographic questionnaire	x		
Gender, age, academic				
qualifications, profession				
mHEART.4U usage	Utilization rate, consulted resources, self-monitoring data		x	x

*T0, Baseline assessment; T1, 3-month intervention assessment; T2, 6-month intervention assessment*.

The primary outcome will be the reduction of recurrent cardiovascular events, which is a composite of (i) cardiovascular rehospitalization or urgent visit; or (ii) unplanned revascularization; (iii) cardiovascular mortality; or (iv) worsening heart failure (29, 30).

Secondary outcomes measures will include:

a) Quality of Life, assessed through the MacNew Heart Disease Health-related Quality of Life (HRQL) questionnaire (MacNew) (31).

Acknowledging the importance of including patient's perspectives on health outcomes, the MacNew is a self-reported questionnaire that has been validated and used with both patients with experience of a myocardial infarction, and patients with experience of angina. The measurement instrument is composed of 27 items, scored from 1 (poor) to 7 (high), to assess global HRQL, physical limitations, emotional and social functions. The MacNew is currently validated to many languages including Portuguese, where it appears to be a reliable, valid and moderately responsive instrument to evaluate HRQL of people after a diagnosis of acute coronary syndrome (32);

b) Adherence to treatment, assessed through the Therapeutic Self-care Scale (TSC) (33).

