### Sample Size Calculation

The sample size calculation for the multicentre clinical trial will be performed in order to allow for a statistically significant comparison between control and intervention groups at each center with a 95% confidence level, two-tailed analysis and aiming at a reduction in the effect variable, i.e., recurrent cardiovascular events, which is a clinically relevant composite of (i) cardiovascular rehospitalization or urgent visit; or (ii) unplanned revascularization; (iii) cardiovascular mortality; or (iv) worsening heart failure (29, 30). The G Power software was used to determine *a priori* sample size according to the evidence reported in a previous systematic review (5), which showed that eHealth CR was effective reducing rehospitalization [RR = 0.49, 95% CI (0.27, 0.89), *p* = 0.02]. Accordingly, a proportion of 6% in the intervention group was rehospitalized compared with 13% in the control group 1 year after the intervention terminus, resulting in an effect size of 7% (5). Departing from this evidence-based measure of effect size, power (1 -β) of 80%, a significance of 0.05 and accounting for 20% loss to follow-up, a sample of 330 patients per arm will be included.

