### Statistical Analysis

The patient characteristics in the two arms at baseline will be compared descriptively using chi-squared tests for the binary and categorical variables and an unpaired Student's *t*-test for the continuous variables. One-sample *t*-test will be performed to measure the differences within the same group.

The primary outcome will be analyzed using a generalized linear mixed model, adjusting for the stratification variables (i.e., gender, hospital unit). Logistic regression will be conducted in order to explore predictive relationships of the baseline categorical variables (e.g., age, clinical variables) on the primary outcomes in both groups.

Analyses to determine the study primary outcome will be performed on the principle of intention-to-treat. Accordingly, assuming there will be a reasonable amount (>5%) of missing data, analyses to determine the primary outcome will be conducted using a multiple imputation model. A per-protocol analysis will be conducted with complete cases to test the robustness of intervention effects under different assumptions. Subgroup analyses will be conducted to determine intervention effects by gender and trial center. All statistical tests will be 2-sided at α = 0.05. The biostatistician will remain blinded throughout the analysis of treatment effects.

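### The exploratory predictor regression labels age and clinical measures categorical and does not say whether it is one model or one per arm; if per arm, the intervention arm has only about 16 to 20 planned events

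*Protocol article*

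**What the plan says.** After the primary model, the Statistical Analysis section of the protocol article adds a logistic regression to "explore predictive relationships of the baseline categorical variables (e.g., age, clinical variables) on the primary outcomes in both groups". It gives no cut-points and no number of predictors. It does not say whether the last three words mean one model per arm or one model over both arms, and it announces no comparison of predictors between arms.

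The same section distinguishes variable types for the baseline table, with chi-squared tests for categorical variables and t-tests for continuous ones. The Outcomes and Measurements section lists blood pressure and blood biomarkers among the clinical data.

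The only event rates are in the Sample Size Calculation section: "a proportion of 6% in the intervention group was rehospitalized compared with 13% in the control group 1 year after the intervention terminus". With "power (1 -β) of 80%, a significance of 0.05 and accounting for 20% loss to follow-up", the section concludes that "a sample of 330 patients per arm will be included". The outcome to be modelled is wider, a "composite of (i) cardiovascular rehospitalization or urgent visit; or (ii) unplanned revascularization; (iii) cardiovascular mortality; or (iv) worsening heart failure", assessed at 3 and 6 months.

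**The concern.** Two features of this one sentence matter.

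First, it classes age and clinical variables as categorical. That is a stated choice, not a detail left out. Age is the first example given. Followed literally, continuous measures would be grouped before modelling. Grouping treats everyone within a category as alike, throws away information and makes the result depend on the cut-points.

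Second, it permits a separate model in each arm. The intervention arm is expected to have the fewer events, so a model with several predictors there would be imprecise and prone to overfitting. Two separate fits also invite a false contrast: a predictor that reaches significance in one arm and misses it in the other looks arm-specific, although no test of that difference has been made.

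At stake is the trial's exploratory account of which patients have events. The primary treatment comparison is not affected.

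**Working it through.** **Inputs.** Rates 6% and 13%, 330 per arm, 20% loss, 80% power (Sample Size Calculation). "All statistical tests will be 2-sided at α = 0.05" (Statistical Analysis). "Participants will be randomized at a 1:1 ratio" (Procedures).

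**1. The plan's own figure.** Pooled-variance formula for two proportions, mean rate 0.095:

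n = [1.96 × √(2 × 0.095 × 0.905) + 0.8416 × √(0.13 × 0.87 + 0.06 × 0.94)]² / 0.07² = (0.813 + 0.346)² / 0.0049 ≈ 274.3, so 275 per arm.

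275 × 1.2 = 330, which matches the stated sample size. With 20% lost, 330 × 0.8 = 264 per arm are observed.

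**2. Planned events** (n × rate).

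| | 264 per arm | 330 per arm |
|---|---|---|
| Intervention, 6% | 15.8 | 19.8 |
| Control, 13% | 34.3 | 42.9 |
| Both arms | 50.2 | 62.7 |

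The binomial 95% range for the intervention arm is 9 to 24 events with 264 patients and 12 to 29 with 330.

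**3. Loss from categorising.** Assumptions: a normally distributed predictor, true odds ratio 1.5 per standard deviation in both arms, 264 per arm, and a median split as the example of grouping. The information on the log odds ratio per standard deviation is approximately the sum over arms of n × p × (1 − p):

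- Intervention: 264 × 0.06 × 0.94 = 14.9
- Control: 264 × 0.13 × 0.87 = 29.9
- Both arms, with a treatment term: 44.7

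A median split of a normal variable keeps about 2/π = 64% of this. Power ≈ Φ(ln 1.5 × √information − 1.96), with ln 1.5 = 0.405:

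- Both arms, continuous: Φ(0.405 × 6.69 − 1.96) = Φ(0.75) ≈ 77%; simulation 75%
- Both arms, median split: information 44.7 × 0.637 = 28.5, Φ(0.405 × 5.34 − 1.96) = Φ(0.20) ≈ 58%; simulation 55%
- Intervention arm alone, continuous: Φ(0.405 × 3.86 − 1.96) = Φ(−0.39) ≈ 35%; simulation 33%
- Intervention arm alone, median split: simulation 19%

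The approximation and the simulated logistic fits agree to within a few points.

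**4. Separate fits and false contrasts.** With a continuous predictor and the same true effect in both arms, simulated power is about 33% in the intervention arm and 58% in control. The arms are independent, so the chance of significance in exactly one arm is 0.33 × (1 − 0.58) + 0.58 × (1 − 0.33) = 0.14 + 0.39 = 0.53. Direct counting in simulation also gives about 53%.

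**5. What a proper comparison could detect.** Assume a binary predictor present in half the patients, with odds ratio 2. The standard errors of the log odds ratio are 0.545 (intervention) and 0.381 (control) at 264 per arm, and 0.487 and 0.341 at 330. The standard error of the difference is √(0.545² + 0.381²) = 0.664, or √(0.487² + 0.341²) = 0.594. For 80% power the ratio of odds ratios must be about exp(2.8 × 0.664) = 6.4, or exp(2.8 × 0.594) = 5.3. Only very large differences between arms could be shown.

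**The case against.** The strongest reply is that the article does not say models will be fitted separately. A single model over both arms fits its words equally well and would have about 50 to 63 planned events. A reader might infer that a per-arm analysis is fixed; the text leaves it open, so the small-event argument is conditional.

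A reader might also conclude that the predictors will be unreliable. That depends on how many are entered together, which the article does not state and which commonly belongs to the analysis plan. The assessment schedule in Table 1 is not a covariate list.

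Nor does the article announce any comparison of predictors between arms, so it cannot be faulted for making an invalid one. It would also be too strong to say that arms cannot be compared: a treatment-by-predictor term allows it, with low power.

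The median split and the odds ratio are assumptions; finer categories would lose less. Calling age categorical may be loose drafting, since the same section handles continuous baseline variables correctly elsewhere. Finally, the regression is described as exploring relationships, so it already claims little.

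All of this stands as a limit on the point. What remains is that the sentence positively describes age and clinical variables as categorical. Whether that is a method or a slip, it needs correcting, and the same edit can settle the model structure.

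**Conclusion.** The point holds in a limited form and is minor. The article states an inferior handling of continuous baseline variables. Under the assumed odds ratio of 1.5 per standard deviation and a median split, that handling costs about 20 percentage points of power in a model over both arms (75% to 55%). It also leaves room for a per-arm analysis. If that is what is meant, the intervention arm offers about 16 to 20 planned events, enough for very few predictors, and about half of trials with identical true effects would show significance in exactly one arm.

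The event counts should not be read as a forecast. They rest on rehospitalization one year after the intervention ended, whereas the trial models a broader composite at 3 and 6 months. Shorter follow-up lowers the count: if event rates were constant and the 6-month risk about half (an assumption), the intervention arm would have about 8 to 10 events. The wider composite raises it. The net direction is unknown.

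Neither the primary estimate nor the sample size is touched.

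**What to change.** Reword the sentence to plan one exploratory logistic model on all randomised patients, containing treatment, gender and hospital unit, with age and other measured variables kept continuous. Keep the number of parameters modest for roughly 50 to 63 planned events, or use a penalised fit; the list of predictors can go in the analysis plan. State that any difference in prediction between arms will be assessed only through a treatment-by-predictor term, and acknowledge that its power will be low.

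The cost is a change of wording, with no new data. The small downside is that fewer predictors can be listed.

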## Discussion

The current study protocol aims to assess the effectiveness of a user-friendly, comprehensive CDSS for remote patient monitoring of CVD patients, primarily on the reduction of recurrent cardiovascular events. To that end a multicentre randomized controlled design involving two cardiology units in the Center Region of Portugal will be conducted involving patients living with CVD and receiving care at these Units. The CDSS will recommend a personalized monitoring plan for each patient through mHealth tools, and provide self-management recommendations adequate to the patient's needs and preferences.

Along with the WHO key global health priority (3) and UN Sustainable Development Goals (4) of reducing CVD-related mortality and morbidity, the mHeart.4U has the potential to contribute to sustainable and person-centerd CR, with low-effort added to the healthcare services and without jeopardizing quality of care (38). The mHeart.4U will be conducted at two cardiology units, which will allow to gain insight concerning contextual differences to the adoption of the intervention. The recruitment and intervention delivery might however entail minor differences that need to be investigated in a *post-hoc* analysis for their potential to induce bias.

Technology-mediated CR has been shown to have equal impact on health outcomes as conventional programmes delivered at the clinic (11). The mHeart.4U trial will primarily study the impact on recurrence of cardiac events, with effects on quality of life being secondarily explored. Along with the increasing importance of meaningfulness of life as a quality indicator for people living with chronic disease, recent trials have had the contrary approach [e.g., (23)]. Although it might be seen as a limitation, the evidence concerning this primary outcome is of paramount importance to ascertain the added value of the mHeart.4U in relation to the existing mHealth-based interventions for cardiac monitoring and rehabilitation, which will integrate the current trial. However, the mHeart.4U trial design does not allow for analyzing the separate effects of different mHealth resources included in the intervention.

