Drop-out rates are recognizably higher in intervention studies involving mHealth resources (10, 15) and the mHeart.4U trial is not immune to that potential limitation. Attempting to mitigate the risk, evidence highlights the importance of attending to psychosocial variables that are related to adherence to mHealth interventions, and contextual factors related to adoption by healthcare professionals (39). As the mHeart.4U will entail personalized recommendations of mHealth resources complementary to standard-of-care, to be used according to the patients' preferences on daily living, the adherence to the intervention is expected to be reinforced.

To the patient participating in technology-based CR, the mHeart.4U is likely to empower to take action while recognizing his/her own resources beyond the disease (23). The patient will naturally become part of the therapeutic partnership in a more equitable role as the healthcare professionals, and his/her agency will be reinforced by the self-monitoring and adherence to self-management recommendation. In such a way, the patient will be more prepared to participate in processes of clinical decision-making (40).

From the healthcare professional's perspective, bridging the gap between the hospital and patient's home is a criterion of quality of care, contributing to enhancing accessibility and care continuity. Among many other advantages, mHealth resources allow to reduce access and continuity inequities related to geographical location and financial constraints. They additionally allow safety of care and treatment along with their telemonitoring resources, with healthcare professionals having access to disease and illness indicators during patient's daily life functioning (17).

The integration of mHealth resources, and particularly the mHeart.4U, into CR will therefore make it possible to personalize the intervention parameters, facilitate monitoring and tracking according to patient's personal preferences and clinical needs, which is expected to improve the patient's recovery and health status (17). This flexibility aspect related to tailoring in mHealth programmes is a valuable feature compared to conventional programmes. Particularly in CR programmes, tailoring is likely to go beyond prompting adherence as the person closer relates to the intervention content and format, to embrace intervention effectiveness as specific e-management recommendations are determined upon the patient's clinical profile.

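### The analysis named to test robustness, per-protocol on complete cases, changes population and missing-data handling together, so it says little about whether the imputed intention-to-treat result is robust

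*Protocol article*

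**What the plan says.** All from the protocol article.

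- **Population (Statistical Analysis):** "Analyses to determine the study primary outcome will be performed on the principle of intention-to-treat".
- **Missing data (same section):** "assuming there will be a reasonable amount (>5%) of missing data, analyses to determine the primary outcome will be conducted using a multiple imputation model". The imputation model is not described.
- **Robustness (same section):** "A per-protocol analysis will be conducted with complete cases to test the robustness of intervention effects under different assumptions". The per-protocol set is not defined and the different assumptions are not named.
- **Other additional analyses:** "Subgroup analyses will be conducted to determine intervention effects by gender and trial center", and in the Discussion a post-hoc look at differences between centres in recruitment and delivery. Both answer other questions.
- **Expected loss:** the Sample Size Calculation section reaches 330 per arm "accounting for 20% loss to follow-up". The Discussion adds: "Drop-out rates are recognizably higher in intervention studies involving mHealth resources (10, 15) and the mHeart.4U trial is not immune to that potential limitation".
- **Outcome source (Table 1):** the primary composite is taken from patient health records and death certificates at 3 and 6 months.
- **Arms (Procedures):** both follow standard treatment; only the intervention arm also receives mHEART.4U.

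**The concern.** A robustness analysis should hold the question fixed and vary one doubtful assumption. Here the question is the effect in everyone randomised, and the doubtful assumption is the one about patients whose outcome is not observed.

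The named check does neither. It swaps the randomised population for a per-protocol set, which in the usual meaning of the term is chosen on behaviour after randomisation. It also replaces imputation by deletion of incomplete cases, which again treats loss as uninformative. If the check disagrees with the primary result, the cause cannot be told apart. If it agrees, that is not evidence that the imputation assumption holds. At stake is a statement in the trial report that the result was tested and found robust.

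**Working it through.** **1. The two analyses side by side**

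| | Primary analysis | Stated robustness check |
|---|---|---|
| Population | All randomised | Per-protocol set (undefined in the article) |
| Missing outcomes | Multiple imputation | Dropped |
| Assumption about loss | Missing at random, if the imputation is of the standard kind | Uninformative given the model covariates |

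The first two rows change together. The third row is not relaxed: deletion asks for no weaker an assumption than standard imputation.

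**2. The plan's own figure.** With 13% v 6%, two-sided 0.05 and 80% power, the mean risk is 0.095 and

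n = [1.960·√(2·0.095·0.905) + 0.842·√(0.13·0.87 + 0.06·0.94)]² / 0.07² = (0.8127 + 0.3465)² / 0.0049 ≈ 274.3, so 275 per arm.

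275 × 1.2 = 330, as stated. Nothing below changes this number.

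**3. Selection with no true effect.** From the document: 13% risk, 330 per arm. Assumed: a share q of the intervention arm is excluded, their risk is k times that of those kept, and all controls are kept. Risk among those kept = 0.13 / [(1 − q) + qk], so RR = 1 / [1 + q(k − 1)].

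| q | k | Risk kept | RR | Two-sided rejection rate |
|---|---|---|---|---|
| 10% | 2 | 11.8% | 0.91 | 7.3% |
| 20% | 1.5 | 11.8% | 0.91 | 7.1% |
| 20% | 2 | 10.8% | 0.83 | 12.5% |
| 20% | 3 | 9.3% | 0.71 | 29% |
| 30% | 2 | 10.0% | 0.77 | 19% |
| any | 1 | 13.0% | 1.00 | 5.0% |

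Rejection rate = Φ[(d − 1.96·s₀)/s₁] + Φ[(−d − 1.96·s₀)/s₁], where d is the risk difference and s₀ and s₁ are the pooled and unpooled standard errors. For q = 20%, k = 2: d = 0.0217, s₀ = 0.0269, s₁ = 0.0266, giving 0.122 + 0.003 = 0.125.

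The direction is not fixed. If those excluded have half the risk (q = 20%, k = 0.5), RR = 1/0.9 = 1.11. If controls are excluded too, at share q′ with the same k, RR = [1 + q′(k − 1)] / [1 + q(k − 1)]. For q = 20%, q′ = 10%, k = 2 this is 1.1/1.2 = 0.92; for q = q′ it is 1.00.

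**4. What a check on loss would show.** Assumed: observed risks of 13% and 6%, 20% missing per arm (66 of 330, leaving 264), lost controls at 13%, lost intervention patients at risk r, and a pooled two-proportion test on 264 per arm. Intervention risk = 0.8·6% + 0.2·r.

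- r = 13%: 7.4% v 13%, p = 0.034
- r = 15%: 7.8% v 13%, p = 0.050
- r = 18%: 8.4% v 13%, p = 0.087

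The tipping point is about 15%, an odds ratio against observed intervention patients of (0.15/0.85)/(0.06/0.94) ≈ 2.8. With 10% missing (297 per arm), p is 0.013 at r = 15% and 0.042 at r = 25%. The per-protocol complete-case analysis produces no such figure, reassuring or otherwise.

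**The case against.** The strongest reply is that the per-protocol analysis decides nothing: the primary test is intention-to-treat with imputation, the sentence openly says the assumptions differ, and a statistical analysis plan that is not shown may add sensitivity analyses. That stands as far as it goes. The absence of other checks is no finding. What remains is that the article assigns the robustness task to an analysis that cannot perform it.

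Four stronger readings are tempting, and the documents do not support them.

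- *Stopping use of the tools biases both analyses in the same favourable direction.* A patient who stops using the tools but whose events are in the records stays in the intention-to-treat analysis. The two analyses would then diverge. Only unobserved outcomes can move both.
- *The document predicts more loss in the intervention arm.* The Discussion remark concerns mHealth studies in general, does not compare the arms of this trial, and is followed by an expectation that adherence will be reinforced.
- *Non-users are compared out against all controls.* The per-protocol set is undefined, and complete cases would drop incomplete controls as well. One-sided exclusion is possible, because only one arm has the tools, but it is an assumption.
- *The primary result is fragile.* In the illustration the tipping point lies above the 13% control risk: lost intervention patients could revert fully to control risk and p would still be 0.034.

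It is also fair that record-based outcomes may be missing less often than the 20% allowance. Selection on adherence would remain even with complete outcomes.

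**Conclusion.** The point holds for the robustness statement and not for the primary test. A per-protocol complete-case analysis is a poor check on an imputed intention-to-treat result: it alters two things at once, may give up the protection of randomisation, and does not probe informative loss.

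In the illustration, selection alone moves a null relative risk to between 0.91 and 0.77 when 10% to 30% of the intervention arm is excluded at twice the risk of those kept. It moves the other way if those excluded are at lower risk, and not at all if exclusion is unrelated to risk or equal in both arms. The exclusion shares and risk ratios are assumptions. The 13% and 6% are the article's planning figures for rehospitalisation one year after the intervention, borrowed here for a six-month composite. The conclusion about the design of the check depends on none of these numbers.

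**What to change.** In the Statistical Analysis section:

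1. Name as the robustness analysis of the primary outcome a delta-adjusted (tipping-point) multiple imputation in all randomised patients. Use the same model as the primary analysis, raise the event odds among intervention patients with missing outcomes in steps, and report the step at which the conclusion changes.
2. Keep the per-protocol analysis, label it supplementary, and delete its stated purpose of testing robustness.

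The cost is a few lines of wording and a little more analysis code. No new data are needed and the 330 per arm does not change. The change should be made before outcome data are seen by arm.
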